##### Cardiorespiratory fitness

We will measure cardiorespiratory fitness using a forty-five second squat test [64]. After a five-minute rest period in a lying position, participants will have to stand up and stay in a standing position for a few seconds until their heart rate (HR) stabilizes. Then they will perform 30 squats in 45 s, following the tempo of 80 beats min^− 1^. The squatting movement will consist of 90° flexion of the knees, keeping the heels on the ground and the back straight, and the arms extended forwards. At the end of the squatting period, participants will lie down and recover for 3 min. The heart rate will be monitored with a HR monitor (Polar®, FT1, Polar Electro, Kempele, Finland). Using HR values at 4 min for the first recovery period, after squatting and after the first minute of recovery (for exact equation, see [64]), the Ruffier-Dickson Index will be calculated and used as a cardiorespiratory fitness index. Validity of this index has been reported by Sartor et al. [64].

#### Control variables

##### Job characteristics

Job characteristics will be assessed with 12 items from the French short version of the Copenhagen Psychosocial Questionnaire [86]. Designed to assess psychosocial risk factors at work, the original version has 46 items grouped in 24 scales referring to six dimensions: quantitative demands, autonomy, organization and leadership, horizontal relationships, work attitudes, and work-related well-being. In this study, we will remove scales that are inappropriate regarding the employment of future participants, and we will assess only one single-item per scale in order to reduce the length of this questionnaire. In addition, we will not measure the work-related well-being dimension which includes scales close to our primary and secondary outcomes. Thus, the “quantitative demands” dimension has three single-items assessing *workload* (“Do you have enough time for your work tasks?”), *work pace* (“Is it necessary to keep working at a high pace?”), and *cognitive demands* (“Does your work require that you remember a lot of things?”). The “organization and leadership” dimension has four single-items assessing *predictability* (“Do you receive all the information you need in order to do your work well?”), *recognition* (“Is your job recognized and appreciated by the management?”), *role clarity* (“Do you know exactly what is expected of you at work?”) and *social support from supervisor* (“Is your supervisor ready to listen to you about work problems”). The “horizontal relationships” dimension has one single-item assessing *social support from colleagues* (“Do your colleagues listen to your problems at work?”). The “autonomy” dimension has two single-items assessing *influence* (“Can you influence the amount of work assigned to you?”) and *possibilities for development* (“Do you have the possibility of learning new things through your work?”). The “work-individual interface” dimension has two single-items assessing *meaning of work* (“Do you feel that the work you do is important?”) and *job satisfaction* (“How pleased are you with your job as a whole, everything taken into consideration?”)*.* Participants will answer these items with a seven-point scale (1 = strongly disagree, 7 = strongly agree). The validity and reliability of this tool were satisfactory and have been reported by Dupret et al. [86].

##### Needs Satisfaction-Frustration at work

The satisfaction versus frustration of the three basic psychological needs at work will be measured using an adapted version of the Needs Satisfaction-Thwarting Scale [87]. It uses a seven-point bipolar response format, each boundary representing the frustration (− 3) versus the satisfaction (+ 3) of a need and the median value (0) corresponding to a neutral sentiment. Following the stem “In the past month, in my work I generally felt...”, participants will be asked to respond to 12 items assessing employee competence (4 items, e.g., “I felt competent (vs. incompetent) at my job”), autonomy (4 items, e.g., “I felt I was free to make my own decisions (vs. I had to follow the decisions that were made for me)”) and colleague relatedness (4 items, e.g., “I felt supported (vs. unsupported by my colleagues”) satisfaction and frustration. This scale demonstrated satisfactory factorial validity and reliability [87]. Using data from the baseline measurements, we will select the three most representative items according to their loading on each of the three factors to assess psychological recovery experiences (see below).

#### Manipulation Check

##### Instructor’s motivating style

To check that PA-NSS instructors display a motivating style that supports participants’ needs more than the PA-TS and the Theatre instructors, we will use measures from objective third-party observers (raters) scoring of the instructors’ motivating style and the participants’ self-reported perceptions of their instructor’s motivating style. To assess the *instructors’ observed motivating style*, all instructors will be recorded audio-visually in the eighth week. Two blinded researchers (i.e., raters) who are familiar with the SDT framework will be trained to score the instructors in terms of need-supportive and controlling motivational style used during the sessions. They will rate the instructors’ motivational style using a modified version of the Interpersonal Support in Physical Activity Consultations Observational Tool (ISPACOT; [88]). This tool assesses supervisors’ behaviors that capture four dimensions of motivational style: *autonomy support* (7 items; e.g., “The instructor encouraged the participants to put forward solutions to barriers”), *competence support* (4 items; e.g., “The instructor gave positive informational feedback to the participants for effort, improvement and task mastery”), *relatedness support* (2 items; e.g., “The instructor demonstrated dedication to and care for the participants”), and *interpersonal control* (8 items; e.g., “The instructor used controlling language with the participants” (e.g., “should, have to, must and ought to”). A seven-point scale (1 = *Not at all true*; 7 = *Very true*) will be employed to rate the degree to which the different behaviors are exhibited. Evidence for the reliability and convergent validity of the ISPACOT have been reported by Rouse [88]. To assess the *participants’ perception of the instructor’s motivating style* participants will be asked to evaluate their instructor’s motivating style during a session, using a slight adaptation of the ISPACOT (e.g., “The instructor listened carefully to how *I* wanted to do things” instead of “The instructor listened carefully to how *the participants* wanted to do things”).

##### PA intensity during sessions

To check that the two PA interventions produce more physical effort than the Theatre intervention, we will assess participants’ *objective* and their *perceived effort*. First, participants in the three intervention groups will be asked to wear a tri-axial accelerometer (ActiGraph LLC, Pensacola, FL, USA; ActiGraph GT3x) on the waist during a session in the sixth week of the intervention. The devices will be initialized with 30 s epochs and the data will be analyzed with Freedson’s algorithm [89]. Moderate to vigorous PA and energy expenditure will be calculated for each participant. Moreover, the *perceived effort* during the sessions will be assessed weekly with one single-item: “How intense was the effort you made during the last session?” (“Very slightly intense” vs. “Very intense”).

#### Weekly measures during the intervention period

During the ten weeks of the intervention period, at the end of the second session each week, all participants in the four conditions will be invited to complete a short questionnaire distributed in an individual booklet (for the PA-TS, PA-NSS, Theatre conditions) or an online (for the WLC condition) format. The questions will assess work-related variables (for all four groups) and intervention-related variables (only for the three intervention groups).

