In addition to the five previous psychological recovery experiences, the *positive affects* that individuals derive from their off-job activities were shown to be related to daily recovery [38]. More precisely, according to the Broaden-and-Build theory [59] and the Conservation Of Resources theory [57], positive emotional states such as happiness or feeling energetic, experienced during off-job activities have the potential to stop the prolongation of negative states built up during the work day, and to build personal resources facilitating the work recovery process. Since meta-analytic data demonstrate that PA is consistently associated with increased energy [60] and positive affects [61], emotional spillover from participation in such activities could be a valuable short-term strategy to promote work recovery [62].

Finally, physiological mechanisms can also be mentioned to explain the beneficial effects of PA. According to the cross-stressor adaptation hypothesis [63], regular PA induces biological adaptations which reduce physiological reactions to all stressors, whether related to PA or more general. Cumulative evidence indicates that employees with higher *cardiorespiratory fitness* (i.e., the maximal aerobic power of an individual, reflected by the maximal oxygen uptake; [64]) regulate and cope more efficiently with their stress [65].

Based on this evidence, we formulate the following hypotheses:*Hypothesis 5:* The effects of the PA intervention on burnout and/or vigor at work are mediated by higher psychological detachment from work (H5a), relaxation (H5b), mastery (H5c), control (H5d), relatedness (H5e), positive affects (H5f) experiences, and cardiorespiratory fitness (H5g).

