### Weekly trajectories of employee burnout, vigor, and psychological recovery mechanisms

Following the recommendations by de Vries and colleagues [29, 66], we will examine the employees’ well-being and recovery trajectories during the course of the trial in order to answer two questions: (a) what is the minimum exposure to exercise or Theatre condition required for burnout and vigor to differ between interventions and control conditions? and (b) are the feeling of having recovered and the experiences of recovery among participants in PA and Theatre condition related to differences in their vigor and burnout trajectories? To be able to answer these questions and provide a finer grain of analysis on the development of well-being indicators during the intervention and on the relationships between these indicators and the recovery mechanisms, during each week of the intervention we will assess the primary outcomes (burnout, vigor) and the psychological mechanisms of recovery (detachment, relaxation, mastery, control, relatedness, and positive affects experiences) using single-item scales. While it is difficult to predict precisely when the well-being indicators will change as a function of the intervention, we nevertheless expect that:*Hypothesis 6a:* Participants in the PA and Theatre conditions report a decrease in feelings of burnout and/or an increase in vigor each week over the intervention period compared to participants in the control condition.*Hypothesis 6b:* Participants in the PA-need-supportive style conditions report a decrease in feeling of burnout and/or an increase in vigor each week over the intervention period compared to participants in the PA-traditional style and Theatre conditions.

Regarding the relationships between recovery and burnout/vigor trajectories, we expect that:*Hypothesis 6c:* Participants in intervention groups who experience greater feelings of psychological detachment from work, relaxation, mastery, control, relatedness, or positive affects experiences during the sessions, show a larger improvement in their weekly burnout and/or vigor trajectories compared to participants who experience lower feelings during these sessions.

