#### Waiting list control condition

During the ten weeks of the three interventions, participants in the WLC condition will not carry out an activity. They will be contacted each week by email to complete an online questionnaire assessing measures similar to those for the three other groups. At the end of the period, they will be offered the possibility of starting the intervention in a delayed group the following year.

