### Measures

Table 1 provides an overview of the measurement points of the primary and secondary outcomes, mediators, moderators and control variables, and manipulation check variables. At the end of the second session of each week, participants will complete a questionnaire measuring their weekly burnout, vigor, needs satisfaction at work and workload, as well as recovery mechanisms experienced, affects and effort perception during sessions (only for the 3 intervention groups). Five minutes are requested to complete the questionnaire. In week six of the program, participants will complete an online survey measuring job characteristics, and intervention groups will wear a 3-axis accelerometer to assess their energy expenditure during PA or theatre sessions. In week eight of the intervention, all instructors will be recorded audio-visually and participants will complete an online survey assessing their instructor’s motivational style during the sessions. At the beginning of the final session of the intervention participants will replicate the cardiorespiratory fitness test, and at the end of the intervention, participants will complete an online survey measuring the same variables as those assessed at baseline. Finally, three and six months after the end of the intervention, participants will be invited to complete the follow-up online questionnaire. In order to measure the *compliance* to the program, instructors from the three intervention groups will be asked to indicate the participants’ presence or absence at each session in a register.

**Table 1 Tab1:** Overview of the measurement points for the primary and secondary outcomes, during intervention and weekly measures, and follow-up measurements

	Variables	Pre-intervention (T0)	During intervention (T6 or T8)	Weekly (T1-T10)	Post-intervention (T11)	Follow-up at 3 and 6 months (T12–13)
Primary outcomes	− Burnout	✓		✓	✓	✓^a^
	− Vigor	✓		✓	✓	✓^a^
Secondary outcomes	− Job satisfaction	✓			✓	✓^a^
	− Work motivation	✓			✓	✓^a^
	− Work performance	✓			✓	✓^a^
	− Work ability	✓			✓	✓^a^
Psychological and physiological mediators	− Off-job recovery activities	✓			✓	
	− Psychological detachment	✓		✓^a^	✓	
	− Relaxation	✓		✓^a^	✓	
	− Control	✓		✓^a^	✓	
	− Mastery	✓		✓^a^	✓	
	− Relatedness	✓		✓^a^	✓	
	− Positive Affects			✓^a^		
	− Cardiorespiratory Fitness	✓			✓	
Moderator variable	− Compliance to activity sessions			✓^a^		
Control variables	− Job characteristics	✓	✓(T6)	✓^b^	✓	

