##### Work-related variables

Employees will be asked to complete a ten-item questionnaire after the second session each week, to assess their weekly *burnout at work* (i.e., three single-items from the SMBM; see above), *vigor at work* (i.e., three single-items from the SMVM; see above), *basic need satisfaction* versus *frustration at work* (i.e., three single-items from the Needs Satisfaction-Frustration at Work Scale; see above), and *workload* (one single-item “How heavy was your workload today?” used by Thøgersen-Ntoumanis et al., [28]). Scores will be rated using a bipolar visual analogue scale of ten centimeters with two opposing anchors (e.g., “never” vs. “always”; “very light” vs. “very heavy”).

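### Weekly burnout and vigor are collected after a session in the activity arms but online by email in the waiting list, which confounds the level part of H6a and the minimum-exposure question

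*Protocol article*

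**What the plan says.** All places are in the protocol article.

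- Measures, on timing: "At the end of the second session of each week, participants will complete a questionnaire measuring their weekly burnout, vigor". The section Work-related variables repeats it: "Employees will be asked to complete a ten-item questionnaire after the second session each week".
- Waiting list control condition: "They will be contacted each week by email to complete an online questionnaire assessing measures similar to those for the three other groups".
- Weekly measures during the intervention period: the form is "distributed in an individual booklet (for the PA-TS, PA-NSS, Theatre conditions) or an online (for the WLC condition) format".
- Work-related variables, on the response scale: "Scores will be rated using a bipolar visual analogue scale of ten centimeters with two opposing anchors". No separate online format is described.
- Hypothesis 6a compares these series directly: "Participants in the PA and Theatre conditions report a decrease in feelings of burnout and/or an increase in vigor each week", relative to the control condition. The same section asks how much exposure is needed before the intervention and control conditions differ.
- Analyses of Weekly trajectories: growth models test the three contrasts on both level and rate of change, adjusting for variables such as weekly need satisfaction and workload.
- Strengths and Limitations: measurement once a week at the second session is presented as a lost chance to compare session days with other days. The difference from the waiting list is not mentioned.

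**The concern.** In the activity arms the weekly score is given minutes after walking or acting, at the session, in a booklet. In the waiting list it is given with no preceding programme activity, away from any session, online. These differences coincide exactly with the first planned contrast, so that contrast on level carries them along with any programme effect.

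The article gives a reason to expect a short-term response: it states that "PA is consistently associated with increased energy" and expects emotional spillover from the activity. The vigor measure covers physical strength and emotional energy. The weekly covariates cannot remove the problem, because they come from the same booklet or online form.

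At stake are the level difference between activity arms and waiting list, and the minimum-exposure answer. A response that lasts only for the hour after a session could appear as a difference already in week one.

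**Working it through.** The plan states no figure for a post-session or mode effect, so there is none to reproduce. The check sets the procedures side by side, derives what a shift does to the planned contrasts, and illustrates its consequence under stated assumptions.

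**1. Procedures by arm**

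| | PA-TS, PA-NSS, Theatre | Waiting list |
|---|---|---|
| Time | end of second session | weekly email; nominally tied to the second session, but this arm has none |
| Form | individual booklet | online |
| Just before | 60-minute session | no programme activity |
| Same sitting | eight activity items, including how the person feels after the session | none of these |

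**2. Effect on the contrasts**

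Codes are from the section on analyses of primary and secondary outcomes. Suppose each activity arm is shifted by δ and the waiting list by 0, with equal arms. A contrast coefficient then moves by Σ(code × shift) / Σ(code²).

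- Waiting list versus the rest: (3 × 0.25δ) / (0.75² + 3 × 0.25²) = 0.75δ / 0.75 = δ. The whole shift enters.
- Theatre versus PA: (−0.667 + 0.333 + 0.333)δ ≈ 0.
- PA-TS versus PA-NSS: (−0.50 + 0.50)δ = 0.

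If δ is the same every week it does not vary with time. It adds to the level term and nothing to contrast × time or contrast × time². If δ changes over the ten weeks, the time terms are affected too.

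**3. Illustration: how often the level contrast is falsely significant**

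Inputs from the article: 35 per group (Sample size), so 35 versus 3 × 35 = 105; ten weekly records (Table 1, T1–T10). Assumptions: no programme effect, weekly SD 1, within-person correlation ρ of 0.5 to 0.7, complete data, two-sided 5% level, constant δ.

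SE = √[(ρ + (1 − ρ)/10) × (1/35 + 1/105)]

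- ρ = 0.5: √(0.55 × 0.0381) = 0.145
- ρ = 0.7: √(0.73 × 0.0381) = 0.167

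Rejection = Φ(δ/SE − 1.96) + Φ(−δ/SE − 1.96). For δ = 0.2, δ/SE is 1.38 or 1.20, giving 28% or 22%.

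| Assumed δ (SD) | 35 per arm | 26 per arm (35 × 0.75) |
|---|---|---|
| 0.1 | 9–11% | 8–9% |
| 0.2 | 22–28% | 18–22% |
| 0.3 | 44–55% | 34–43% |
| 0.5 | 85–93% | 73–85% |

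At a 2.5% level with 35 per arm the figures are 5–6%, 15–20%, 33–43% and 78–89%. The formula is symmetric, so a shift the other way is equally disruptive.

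**4. Simulation**

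A mixed model with random intercept and slope and linear time was fitted to waiting list versus the rest, with no programme effect and 120 runs per row. The assumed shift lowers burnout. In the rows with selective absence, the log odds of attending, and hence of completing the form, fall by 0.7 per SD of that week's burnout.

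| Scenario | Level bias (SD) | Level rejected | Slope bias |
|---|---|---|---|
| No shift, absence unrelated to burnout | 0.00 | 7.5% | 0.00 |
| Selective absence only | −0.10 | 12.5% | 0.00 |
| Shift 0.3 only | −0.31 | 56% | 0.00 |
| Both | −0.40 | 81% | 0.00 |

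With 120 runs the standard error near 5% is √(0.05 × 0.95/120) = 2.0 points, so 7.5% in the first row is compatible with 5%.

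**The case against.** - **Timing.** The section on weekly measures invites all four arms at the end of the second session, so a reader should not infer that the waiting list answers at any time it likes. That is right, and the email day may be fixed in the full protocol. It does not help much: even a simultaneous email reaches people who have not just taken part in a session.
- **What H6a tests.** H6a is mainly about change over the weeks, and a constant shift leaves the time terms alone. This stands and limits the point to level and minimum exposure.
- **Direction.** A reader might infer that the programme must look too good. The documents do not support that. Energy and affect may rise, but burnout includes physical fatigue, which could score worse straight after a walk.
- **Item wording.** The items concern weekly burnout and vigor at work, and momentary affect has its own items. This may dampen the influence of the session but cannot be relied on to remove it.
- **Theatre.** A reader might extend the point to PA versus Theatre. Both use the booklet at the same point in the week. A different immediate response to walking and acting would be a difference between activities, not a measurement split.
- **Missing data.** A reader might infer that anyone absent from the second session has no record that week, and that absence follows a bad week at work. The article says neither; it gives no procedure for absentees, which an article may condense. The concern is conditional on that.

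**Conclusion.** The point holds in a limited form. The level difference between activity arms and waiting list in H6a, and the minimum-exposure question, confound any programme effect with post-session state and response mode. The article does not acknowledge this. The contrast-by-time terms are unbiased as long as the shift is constant over weeks. H1–H4 are unaffected, because the pre, post and follow-up scores come from online surveys.

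The size cannot be taken from the documents. The rejection rates above rest on an assumed shift, SD and correlation, and show only that a modest shift would be enough to matter. It is tempting to express such a shift as a share of the planned d = 0.35. That would mislead, because the article does not tie this effect size to the weekly visual analogue scores. If absentees receive no form, missingness would also depend on attendance in the activity arms only; this is an inference from the article's silence.

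**What to change.** 1. Send the ten work-related weekly items (burnout, vigor, need satisfaction, workload) to all four arms by the same email link, on one fixed day that is not a session day, whether or not the person attended. Keep the eight activity-related items in the session booklet. This aligns timing, setting and mode, and separates completion from attendance.
2. Enter the T0 burnout or vigor score as a covariate in the weekly growth models. It is already collected. It adjusts the level comparison for starting differences but does not remove a post-session shift, so it does not replace the first change.

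The email survey already runs for the waiting list and no items are added. The cost is a second short weekly completion for about 105 activity-arm participants, in a trial that already cites its measurement load, and possibly lower response than at the session.

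If collection has already begun, base H6a on the contrast-by-time terms. State in Strengths and Limitations that level differences and minimum exposure against the waiting list may reflect post-session or mode effects.
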